# The clinical efficacy of Shi-style lumbar manipulations for symptomatic degenerative lumbar spondylolisthesis: protocol for a randomized, blinded, controlled trial

**DOI:** 10.1186/s13018-019-1214-x

**Published:** 2019-06-14

**Keywords:** Chiropractic manipulations, Degenerative lumbar spondylolisthesis, Shi-style lumbar manipulation, Mechanical lumbar traction, Randomized controlled trial

## Abstract

**Background:**

Symptomatic degenerative lumbar spondylolisthesis (DLS) presents spinal problems in daily life. Shi-style lumbar manipulation (SLM), as an alternative treatment for DLS, is popular in China. SLM is based on the channels and collaterals theory of the traditional Chinese medicine, in which the symptoms are believed to result from channel blockage and joint displacement. However, there is no solid evidence to show the effect of the SLM on the management of symptomatic DLS.

**Methods/design:**

We conduct a prospective randomized, blinded, controlled trial to compare the effectiveness of SLM with mechanical lumbar traction and explore whether it could be a potential therapy for symptomatic DLS. A total of 60 patients with symptomatic DLS will be enrolled and treated with the SLM or mechanical lumbar traction for 2 weeks. VAS score and SF-36 questionnaire were assessed at baseline and at 2, 4, 12, and 24 weeks. Any signs of acute adverse reactions, such as lower limb paralysis or syndrome of cauda equina, will be recorded at each visit during treatment.

**Discussion:**

Although the SLM has been used in China for many years to treat symptomatic DLS, there is a lack of consensus about its effectiveness. This trial will provide convincing evidence about the effect of SLM on symptomatic DLS.

**Trial registration:**

Registered on 6 January 2019; the trial number is ChiCTR1900020519.

**Electronic supplementary material:**

The online version of this article (10.1186/s13018-019-1214-x) contains supplementary material, which is available to authorized users.

## Introduction

Symptomatic degenerative lumbar spondylolisthesis (DLS) presents spinal problems in daily life [1]. The osteoarthritic and degenerative changes in disc, facet joints, and ligament cause spinal stenosis and result in mechanical low back pain and radiating pain in buttock and legs. Currently, degenerative lumbar spondylolisthesis is treated with both surgical and non-surgical methods. Surgical intervention is applied for patients with severe pain or progressive neurologic deficits. The non-surgical/conservative management (e.g., NSAIDS drugs, physical therapy, or chiropractic manipulations) is usually applied in the first instance [2, 3].

Shi-style lumbar manipulation (SLM), as an alternative treatment for DLS, is popular in China. SLM is based on the channels and collaterals theory of the traditional Chinese medicine, in which the symptoms are believed to result from channel blockage and joint displacement [4, 5]. Despite its popularity in China, few studies have investigated the effectiveness of Shi-style manipulations in the management of chronic low back pain. Therefore, this prospective, randomized, controlled clinical trial aims to compare the effectiveness of SLM with mechanical lumbar traction and explore whether it could be a potential therapy for symptomatic DLS.

## Materials and methods

### Study design

This study is a prospective, outcome assessor-, and data analyst-blinded randomized controlled clinical trial. The objective of this proposed study is to investigate whether SLM could lead to an improvement in DLS patients. The principal investigator (PI) is responsible for the overall project and organizing of steering committee meetings. PIs of sub-center departments are responsible for gathering experts to carry out the project. An independent steering committee will be responsible for affairs such as participants’ safety, meetings, recruitment and follow-up of participants, and quality control. The coordinating center is responsible for communicating protocol modifications and providing materials. This trial includes a 2-week treatment period and a 6-month follow-up period. After randomization, patients will receive 6-session treatment over a period of 2 weeks. Outcome assessments will be conducted at baseline, as well as at 2, 4, 12, and 24 weeks (Fig. 1; Additional file 1).

**Fig. 1 Fig1:**
[figure not shown]
Study flow

### Eligibility criteria

#### Inclusion criteria

Participants who meet the criteria below are eligible [6, 7].Adults (aged ≥ 18 years) with DLSMeeting the diagnostic criteria for DLS (The North American Spine Society, NASS)Having persistent symptoms for more than 12 months before enrollmentBeing willing to give informed consent

#### Exclusion criteria

The exclusion criteria are as follows [6, 7]:DLS combined with neurological diseases, such as polio, Guillain-Barre syndrome, and myastheniaImaging examination indicating pedicle fissure, tuberculosis, or spine fractureDLS combined with systemic diseases, such as malignant tumors, diabetes, severe rheumatism, or severe osteoporosisLumbar surgery before enrollmentFailure to understand or sign informed consent

### Patient population and recruitment procedure

Participants will be recruited from Longhua Hospital affiliated with the Shanghai University of Traditional Chinese Medicine. Prospective participants will be interviewed by the coordinators and informed of the eligibility criteria and the procedure. Those who are eligible and willing to participate in the study will be screened initially by baseline assessment and then diagnosed based upon clinical manifestations, physical examination, and imaging. Participants will be informed that participating in the trial was absolutely voluntary and withdrawal from the trial can be made at any time. In case of withdrawal, the data collected will not be deleted and will be used in the final analyses. A data compilation form including all variables of interest and all potential risks will be completed by the corresponding research center. The information obtained will be stored in an electronic database for subsequent statistical analysis. Recruitment will start in January 2019 and is expected to end in July 2020. The final follow-up of all participants will be completed on 31 December 2020. The overview of the participant processing and the schedule of evaluation is provided in Fig. 1.

### Ethics

This study will be conducted in accordance with the principles of the Declaration of Helsinki for Clinical Research [8]. The trial protocol has been approved by the Research Ethical Committee of Longhua Hospital, affiliated to Shanghai University of Traditional Chinese Medicine, Shanghai, China (approval number: 2018LCSY058). All participants will be given sufficient time to reach a decision to sign the consent form prior to the study [9, 10]. And the protocol has been registered on Clinical Trials (ClinicalTrials.gov, ID: ChiCTR1900020519).

### Intervention

Because of the nature of the intervention, the patients and therapists could not be blinded to each other. The patients will be treated with Shi-style lumbar manipulations or mechanical lumbar traction, for 6 sessions over 2 weeks. The patients will be asked to note their drug use (including over-the-counter analgesics) after randomization.

### Shi-style lumbar manipulations

#### Tendon soothing

The therapist makes circular and rhythmic motions with the palm on the back of the waist for 3 min, and then presses with the palm root along the median line of the patient’s spine on both sides of the body for 3 min.

#### Osteopathic manipulation

The patient lies in the prone position. The assistant pulls the patient’s ankle back and upward, and then shakes the ankle up and down, while the therapist presses the waist of the patient lightly and flexibly for 3–5 times.

#### Collateral dredging

The therapist presses the bilateral sacrospinous muscles for 2–3 min, and then slightly shakes the patient’s ankles up and down with small amplitude and high frequency for 2 min.

### Mechanical lumbar traction

The traction treatment was based on the “Guidelines for diagnosis and treatment, and rehabilitation of DLS (2017)”. The patient receives 6 sessions of 30-min mechanical persistent lumbar traction over 2 weeks. The patient lies in a prone position. The traction angle was 0°. All procedures are performed with the patient’s comfort ensured. The traction force starts at 10 kg and increases by about 2 kg each visit, depending on centralization or reduction of symptoms. The maximum force used is 20 kg.

### Randomization and allocation

After the screening, patients will be randomized into two groups with an allocation ratio of 1:1. The randomization will be generated via SAS PROC PLAN software (SAS Inc., Cary, NC, USA) by an independent third-party clinical research organization (Institute of Basic Research in Clinical Medicine, China Academy of Chinese Medical Science) and concealed from the researchers by a senior data manager who is not involved in the study. The group assignment list will be sealed in opaque envelopes and be opened by the researchers following informed consent procedures and baseline testing.

### Blinding

All the investigators, physicians, nurses, assessors, analysts, and participants will be blinded to the group assignment until the end of the trial, when all statistical analyses are finished. The patients will not be blinded. If, after the first administration, any clinically significant adverse event potentially related to the treatment occurs, the study physician will re-evaluate the participant, and PI will decide whether the non-blinded procedure is necessary. If non-blinding is required, the allocation information will be provided.

### Outcome measurements

#### Primary outcome measurements

As pain is the most frequent complaint of DLS patients, we choose the VAS score as the primary outcome measurement to assess the low back pain and leg pain. VAS, a reliable and valid measurement of pain, has a horizontal, 100-mm-long line, with “no pain” recorded on the left side (score, 0) and “pain as bad as it could be” on the right side (score, 10). Patients are asked to place a hatch mark that corresponds to their current level of pain (both at rest and at most painful movement) on the line [11]. The VAS score is then determined by measuring the distance between the left endpoint and the point that the patient marked.

#### Secondary outcome measurements

The Oswestry Disability Index (ODI), one of the most widely used gold standards of outcome measurement in patients with low back pain, has been used for more than 25 years. ODI score is calculated by doubling the sum of the scores from the 10 sections and is reported as a percentage of the patient’s perceived disability.

Health-related quality of life will be measured using the SF-36 questionnaire, which is widely used to assess the quality of life for DLS patients. The SF-36 questionnaire is a tool for assessing physical status, consists of 36 items, and measures in seven dimensions: physical functioning, bodily pain, general health perceptions, physical role functioning, emotional role functioning, social role functioning, and mental health. It has been found reliable and valid in many patient populations [12, 13].

### Safety assessments

To assure the safety of participants, the data collection process will be supervised by the project director. At each visit, participants need to stay in the hospital for 30 min after the treatment and will be asked about the adverse effects for any signs of acute adverse reactions during the study period, such as lower limb paralysis or syndrome of cauda equina. Side effects will be recorded at each visit during treatment.

### Statistical analyses

Prior to all analyses, a detailed statistical analysis protocol will be developed. All data will be analyzed in the clinical research center of Longhua Hospital affiliated to Shanghai University of TCM by statisticians blinded to allocation using the SPSS 20.0 statistical software (SPSS Inc., Chicago, Illinois). Efficacy and safety analyses will be conducted according to the intention-to-treat principle using the “last observation carried forward” rule. Before randomization, baseline characteristics will be collected as descriptive statistics for each patient, including gender, age, BMI, duration of symptoms, and degree of lumbar spondylolisthesis. The data analysis of the primary outcome is based on the per-protocol population as a supportive analysis. Mean, standard deviation, median, quartiles and inter quartiles for continuous variables, and frequency for categorical variables will be calculated. Continuous variable followed the normal distribution will be presented as means with standard deviations (SDs) and calculated by an independent sample Student’s *t* test; otherwise, the data will be expressed as medians with ranges, and non-parametric tests will be used. Categorical variables will be expressed as number (%) and analyzed by *χ*^2^ test or Fisher’s exact test. Repeated measurement analysis of variance will be used to analyze value changes of VAS, ODI, and SF-36 scores in the different time points (baseline, week 1, 2, 4, 12, and 24) in the test. A *P* value of less than 0.05 is defined as statistical significant with two-sided 90% confidence intervals (CIs). Missing data will be input with the last observed response carried forward for all measures using the “last-value-carried-forward” principle.

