### Data collection and monitoring

This is a 24-week clinical trial in which participants need to take research intervention for 2 weeks with 24 weeks’ follow-up. Five rounds of disease activity assessments (at baseline and at 2, 4, 12, and 24 weeks) and six rounds of safety assessments (at baseline and at 1, 2, 4, 12, and 24 weeks) will be recorded in Epidata (Version 3.1) by two statisticians independently. Disagreement will be solved by discussion and a third statistician. Longhua Hospital affiliated to Shanghai University of Traditional Chinese Medicine is responsible for monitoring and quality control.

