## Discussion

DLS is a common spinal disease. Currently, there is not enough evidence based on the strict clinical trial of evidence-based medicine (EBM) because of the poor quality of current studies, for example, small sample size, no description of methods for randomization, and no standardized protocol which may lead to performance bias. Based on the theory of dynamic and static disequilibrium in TCM, manipulations have been proved more effective in treating chronic low back pain than other therapies such as analgesics, NSAIDs, or muscle relaxants. SLM, as one traditional Chinese exercise, has shown its efficacy in relieving DLS symptoms.

To our best knowledge, our study is the first elaborately designed, randomized, controlled trial to investigate the efficacy of manipulations in treating symptomatic DLS with clear standards. It is designed as a comprehensive study of pain relief, functional outcome, and adverse effects. Outcome measurements are widely used in research of symptomatic DLS to establish baselines, evaluate the effect of an intervention, and motivate patients’ self-evaluation. The VAS measurements, which have been found valid, reliable, and easy to apply in researches, are often used as the criterion standard to evaluate the pain intensity. The SF-36, a self-administered questionnaire, has been widely adopted as the criterion standard to estimate disease activity for its reliability and validity. Therefore, for the self-effectiveness assessment, we use the VAS for self-assessment of pain and SF-36 for self-assessment of function [15, 16]. The safety of SLM will be assessed by patients’ self-reporting of their quality of life and symptoms, such as lower limb paralysis or syndrome of cauda equina.

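### Safety is tied to the intention-to-treat set, so never-treated patients stay in the harm denominator and harms are counted by assigned arm; a safety table by treatment received should be added

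*Protocol article*

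**What the plan says.** The Statistical analyses section sets one rule for both kinds of outcome: "Efficacy and safety analyses will be conducted according to the intention-to-treat principle", with last observation carried forward. It later repeats the filling rule without exempting safety: "Missing data will be input with the last observed response carried forward for all measures".

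The only other analysis set is per-protocol, and it is confined to the primary outcome: "The data analysis of the primary outcome is based on the per-protocol population as a supportive analysis". No section defines a safety set or groups patients by treatment received.

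The Safety assessments section has participants in both arms asked about "any signs of acute adverse reactions during the study period, such as lower limb paralysis or syndrome of cauda equina". The Discussion links the same two events to the manipulation: "The safety of SLM will be assessed by patients’ self-reporting of their quality of life and symptoms".

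Under Randomization and allocation, "patients will be randomized into two groups with an allocation ratio of 1:1", and the envelopes are opened after consent and baseline testing. Under Patient population and recruitment procedure, patients may withdraw at any time and their data stay in the final analyses. Quality control provides for recording drop-outs, withdrawals and compliance. It does not explicitly list the treatment or number of sessions received.

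**The concern.** For a superiority claim on efficacy, intention to treat is the cautious choice, because non-adherence usually pulls the arms together. For harms that arise from a physical procedure, the same property is not cautious. A patient who never had a session was not exposed to the procedure but still enlarges the denominator. A patient who had the other procedure was exposed to that one, but an event would be listed under the assigned arm.

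The trial has two arms of 30 or 36 patients and is meant to inform guidelines on the safety of the manipulation. With so few patients, any serious harm will be counted in ones and twos. The safety statement may also rest on zero events and an upper confidence limit, which depends directly on the denominator.

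This is a rule the article states, not a detail left open. An analysis plan that follows it would carry the same safety population forward.

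**Working it through.** The plan gives no harm rate or safety precision figure to reproduce. The check asks how the stated rule changes the reported rate.

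**Inputs from the article**
- Patients per arm: 36 (Sample size calculation, 72 in total). The Abstract gives 60 in total, that is 30 per arm, so both are shown.
- Dropout: 20% (Sample size calculation), with no split into before and after the first session. 0.20 × 36 = 7.2, about 7 per arm; 0.20 × 30 = 6 per arm.

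**Assumption**
- The number never treated per arm, m, is not given. The range is 0 to 7 on 36 and 0 to 6 on 30. The upper end places all of the planned dropout before the first session.

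**1. Absolute rate.** With x events among treated patients, the treated-patient rate is x/(N − m) and the intention-to-treat rate is x/N. Their ratio is (N − m)/N.

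| N | m | Ratio | One-sided 95% upper limit with zero events, all N | Same, treated only |
|---|---|---|---|---|
| 36 | 0 | 1.00 | 8.0% | 8.0% |
| 36 | 1 | 0.97 | 8.0% | 8.2% |
| 36 | 2 | 0.94 | 8.0% | 8.4% |
| 36 | 4 | 0.89 | 8.0% | 8.9% |
| 36 | 7 | 0.81 | 8.0% | 9.8% |
| 30 | 6 | 0.80 | 9.5% | 11.7% |

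The upper limit for zero events in n patients is 1 − 0.05^(1/n). For n = 36 this is 0.0798, and for n = 29 it is 0.0981. With two events and m = 7, the rates are 2/36 = 5.6% and 2/29 = 6.9%.

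**2. Relative risk.** If m1 and m0 patients are never treated in the two arms, the intention-to-treat relative risk equals the treated-patient relative risk times (36 − m1)/(36 − m0).
- Equal fractions: the factor is 1, so the relative risk is unchanged and only the absolute rates and their difference shrink.
- Most unequal case in the range: 29/36 = 0.81 if all 7 are in the manipulation arm, or 36/29 = 1.24 if all 7 are in the traction arm. The distortion can run either way.

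**3. Crossover, hypothetical only.** If c patients in each arm receive the other treatment, the risk difference is multiplied by (36 − 2c)/36: 0.94 for c = 1, 0.89 for c = 2, 0.78 for c = 4. As an illustration of attribution, take two harms after manipulation, one of them in a patient assigned to traction who received manipulation, with no other crossover. Intention to treat shows 1/36 against 1/36; grouping by treatment received shows 2/37 against 0/35.

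**4. Carrying values forward.** The Data collection and monitoring section includes a baseline safety round. A never-treated patient may have that round as the only record. Under the stated rule it can be carried forward as no event, which makes the dilution in step 1 explicit.

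**The case against.** Analysing harms by randomised arm is legitimate. It keeps the randomised comparison and describes harm under an assigned strategy. This stands, and it is why the intention-to-treat table should be kept. It does not justify having no table of treated patients, because the rate among those who received the procedure is also needed.

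The article also announces a detailed analysis protocol, in which a safety set is commonly defined. This is only a partial answer, because the article has already named intention to treat for safety.

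The strongest objection concerns size, and it stands. Treatment lasts two weeks and follow-up runs to week 24, so much of the 20% dropout may come after treatment. With one never-treated patient per arm, the ratio is 0.97.

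A reader might infer that switching is to be expected, since patients know their arm and the Introduction calls the manipulation popular. The documents do not support that. No section describes switching, the course is six sessions in two weeks, and supervisors check adherence twice a month. A reader might also infer that the rule could reverse the safety conclusion. That needs an invented patient, and a table of 0/36 against 1/36 has a Fisher p value of 1.0, so it would support no comparative conclusion.

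**Conclusion.** The point holds as a cheap improvement. The plan fixes safety on the intention-to-treat set and provides no table of treated patients. Allocation precedes the first session, so never-treated patients can lower the reported absolute harm rates and tighten the upper limit when no event is seen.

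The size is conditional on the assumed 0 to 7 never treated among 36. The lowest ratio, 0.81, and the gap between 8.0% and 9.8% are the extreme of that range, not an expected value. On the 30 per arm implied by the Abstract, the extreme is 0.80.

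Two stronger readings are not supported. One is that the rule always favours the manipulation: equal never-treated fractions leave the relative risk unchanged, and unequal ones can move it either way. The other is that harms will in fact be credited to the wrong arm: the rule would do so if patients crossed over, but nothing in the article shows that they will. If all patients receive the assigned treatment, there is no distortion.

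**What to change.** Keep intention to treat for efficacy and replace the safety part of the sentence with wording such as:

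> Safety will be analysed in all patients who received at least one session of either treatment, grouped by the treatment actually received, using observed events without carrying values forward. A safety table by randomised arm in all randomised patients will be given alongside.

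Make sure the case report form records the treatment received and the number of sessions, since Quality control names only drop-outs, withdrawals and compliance.

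The cost is one revised sentence, one extra table and a check of the form, with added fields if they are not already there. Patients who receive sessions of both treatments need a grouping rule, which should be set before harms are seen by arm. The downside is that the comparison by treatment received is not strictly randomised; the accompanying intention-to-treat table covers this.

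### The repeated-measures ANOVA lists a week-1 efficacy time point that the schedule does not collect, and treats baseline as an outcome level while no stated analysis adjusts for it

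*Protocol article*

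**What the plan says.** Statistical analyses: "Repeated measurement analysis of variance will be used to analyze value changes of VAS, ODI, and SF-36 scores", with the time points given as "in the different time points (baseline, week 1, 2, 4, 12, and 24) in the test". The section does not say whether group, time or group-by-time is the treatment test. For normally distributed continuous variables it adds that they are "calculated by an independent sample Student’s *t* test", with non-parametric tests otherwise. No covariate is named. On missing values: "Missing data will be input with the last observed response carried forward for all measures". A more detailed analysis document is announced but is not shown.

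The outcome schedule appears in three other places:

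- Study design: "Outcome assessments will be conducted at baseline, as well as at 2, 4, 12, and 24 weeks".
- Abstract, Methods/design: "VAS score and SF-36 questionnaire were assessed at baseline and at 2, 4, 12, and 24 weeks".
- Data collection and monitoring: "Five rounds of disease activity assessments (at baseline and at 2, 4, 12, and 24 weeks"), set against "six rounds of safety assessments (at baseline and at 1, 2, 4, 12, and 24 weeks").

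**The concern.** There are two linked problems.

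First, the analysis calls for efficacy values at a visit where none are planned. Three sections agree on five efficacy times. The Statistical analyses section lists six, and its list is identical to the safety schedule. An analyst following the text has either no week-1 value for anyone, or a week-1 value manufactured from baseline by the carry-forward rule.

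Second, baseline sits among the response levels. Under Randomization and allocation, the envelope is opened after baseline testing, so the expected group difference at baseline is zero. A test that averages over all levels mixes that zero into the treatment effect. A test of group-by-time avoids this but does not use baseline efficiently. The other stated comparison, the t test or its non-parametric substitute, is unadjusted.

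At stake are an efficacy model that can be run on the collected data, a clear estimand, and precision in a trial of about 30 to 36 patients per arm.

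**Working it through.** **1. Visit lists.**

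| Source | Times (weeks; 0 = baseline) |
|---|---|
| Statistical analyses, ANOVA of VAS, ODI, SF-36 | 0, 1, 2, 4, 12, 24 |
| Study design; Abstract; Data collection (efficacy) | 0, 2, 4, 12, 24 |
| Data collection (safety) | 0, 1, 2, 4, 12, 24 |

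The ANOVA list minus the efficacy list leaves week 1 only. If week 1 is filled from baseline, the week-1-minus-baseline difference is zero for every patient. That contrast has no variance, so a multivariate within-subject test on all six levels cannot be computed.

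**2. Size of the group main effect.** Let the true difference be *d* at each of the four post-baseline visits and 0 at baseline. The main effect is the average over levels.

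- Five collected times: 4*d*/5 = 0.80*d*.
- Six times with week 1 copied from baseline: 4*d*/6 = 0.67*d*.

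For scale, the pilot changes under Sample size calculation give *d* = 4.56 − 2.34 = 2.22. The averages are then 1.78 and 1.48. For group-by-time, baseline is the reference for change and no such shrinkage occurs.

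**3. Precision against a single-visit t test.** With equal variance σ² at both times and correlation *r*, a change score has variance 2σ²(1 − *r*). Baseline adjustment gives σ²(1 − *r*²), ignoring one degree of freedom. The ratio is (1 + *r*)/2:

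- *r* = 0.3: 0.65, a 35% cut
- *r* = 0.5: 0.75, a 25% cut
- *r* = 0.7: 0.85, a 15% cut

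The text does not say whether the t test is on change or on raw follow-up scores. Against raw scores the ratio is 1 − *r*², or 0.91, 0.75 and 0.51.

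**4. Power, as ranges.** The article gives no SD and no correlation, so both are assumed. I used compound symmetry, a constant *d* = 2.22, two-sided 5%, and noncentral F. The variances are:

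- Five-level mean: σ²(1 + 4*r*)/5.
- Six-level mean with filled week 1 (weight 2/6 on baseline, 1/6 on each later visit): σ²[*r* + (1 − *r*)·8/36].
- Mean of four visits adjusted for baseline: σ²[(1 + 3*r*)/4 − *r*²].

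Group-by-time over five visits has noncentrality (*n*/2)(4*d*²/5)/[σ²(1 − *r*)] on 4 and 4(2*n* − 2) df.

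Example at σ = 2.6, *r* = 0.5: standardised effects are 1.48/2.03 = 0.728 (filled), 1.776/2.01 = 0.882 (five levels) and 2.22/1.59 = 1.394 (adjusted).

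Ranges over σ = 2.0, 2.6, 3.0 and *r* = 0.3, 0.5, 0.7:

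| Test | 28.8 per arm (36 less 20%) | 36 per arm |
|---|---|---|
| Main effect, week 1 filled | 56% to 98% | 65% to >99% |
| Main effect, five times | 72% to >99% | 81% to >99% |
| Group-by-time, five times | 65% to >99% | 76% to >99% |
| Baseline-adjusted mean of four visits | >99% | >99% |

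The 36-per-arm column treats carried-forward values as if they were observed.

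With a smaller assumed effect of 0.5 SD per visit and 30 per arm, at *r* = 0.3 / 0.5 / 0.7:

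- Main effect, five times: 63% / 50% / 42%
- Group-by-time (4 df): 34% / 46% / 71%
- Mean post-baseline change from baseline (1 df): 53% / 67% / 87%
- Baseline-adjusted mean of four visits (1 df): 87% / 88% / 95%

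Part of the gap to group-by-time comes from spending 4 df on an omnibus test. The gap between the last two lines comes from baseline adjustment alone.

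The article has no figure of its own on this point to reproduce; the origin of its sample size is a separate matter.

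**The case against.** A reader might infer that the plan dilutes the treatment effect as a matter of fact. The text does not support that. It names no term, and an ANOVA described as analysing changes in value over time fits group-by-time at least as well, where nothing is diluted. With *d* = 2.22, SD 2.6, *r* = 0.5 and 28.8 per arm, group-by-time has about 92% power, and a single-df contrast of the post-baseline mean with baseline about 98%.

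A reader might also infer that the trial is underpowered, by quoting the 78% main-effect power that those inputs give with week 1 filled. That requires an analyst to create a week-1 column that no efficacy form collects, fill it, and then test the main effect. A visit never scheduled is not obviously missing data, and the more likely result of the slip is a five-level analysis, at about 91%. The 28.8 also sits badly with an intention-to-treat analysis using carry-forward, which keeps all 36; the two figures then become 86% and 96%.

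Finally, unadjusted comparisons are unbiased under randomisation, and covariates are often left to the analysis plan, which is not shown.

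These objections stand against the unconditional bias claim and any single power figure. They do not remove the contradiction in visit lists. Nor do they change the fact that this text places baseline among the response levels, a choice it states rather than leaves open.

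**Conclusion.** The point holds in a limited form. The week-1 efficacy time point contradicts three other sections and is wrong as written. Baseline is written as an outcome level, and no stated analysis adjusts for it.

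The loss is conditional. The effect estimate shrinks to 80% (five times) or 67% (week 1 filled) only if the group main effect is the treatment test and the effect is constant after baseline. Under group-by-time the cost is power, not bias. Under the assumptions shown, the baseline-adjusted analysis was at least as powerful as the alternatives throughout, but the size of the gain depends on an SD and correlation that the article does not give. If the effect is concentrated at one visit, the average over four visits is a less favourable contrast than these figures suggest.

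The documents do not establish that the trial will be biased toward zero or will miss its power target.

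**What to change.** - Delete week 1 from the efficacy time points in Statistical analyses, so that the list agrees with the Abstract, Study design and Data collection sections. If week-1 efficacy data are in fact intended, add them to those sections instead.
- Analyse weeks 2, 4, 12 and 24 as responses, with treatment, visit, treatment-by-visit and the baseline score as covariate.
- Name the one treatment contrast that is the primary test: the difference at a stated visit, or the average over stated visits.
- If a mixed model is used, say how it relates to the carry-forward rule. Such a model can use incomplete records without single imputation, so the text should say whether carry-forward stays as the main approach, becomes a sensitivity analysis, or is dropped.
- Show any supporting power figure over a range of SDs and correlations.

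The cost is protocol and analysis-plan wording and a little analysis work. No new visits, data or patients are needed.
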